### Phase 1: Evaluation of effect

Research question:

1. Does a multi-component care transition intervention have an effect on perceived quality of care transitions, health literacy, collected medications, medication adherence, perceived person-centeredness, functioning, recurrent stroke/TIA, healthcare utilization and caregiver burden?

#### Setting

The intervention will be conducted in the Stockholm region at one acute stroke unit and one geriatric stroke ward and will involve the corresponding neurorehabilitation teams in primary care. Another acute stroke unit and geriatric stroke ward, with the corresponding neurorehabilitation teams in primary care, will serve as control sites. Patients at the control sites will receive standard care transitions. Based on our pre-studies, “standard care transitions” means that the care transition is initiated by an electronic referral from allied health professionals at the hospital to the receiving neurorehabilitation team. The referral notifies the neurorehabilitation team about the patient’s discharge. The teams are then obliged to contact the patient within 48 hours after hospital discharge. Further, a discharge meeting is held with the patient and responsible physicians. Patients receive a standard discharge letter and an informational leaflet about the neurorehabilitation team.

#### Participants

*Patients*. We will include patients who have had a first time ever, or recurrent, stroke or TIA who are to be discharged from the participating hospitals to home and referred to a neurorehabilitation team for continued rehabilitation. The patients must be able to give informed consent by themselves. The patients will be informed of the study and invited to participate at the hospitals by a research assistant. The research assistant will provide oral and written information about the study and will obtain informed consent from the patients who agree to participate.

*Significant others*. The included patients will be asked if they are willing to name a significant other for invitation to participate in the study. The significant others will be mailed written information about the study, including an informed consent form and a pre-stamped envelope. Significant others who return a signed consent will be included in the study. Patients will remain included if they do not have or do not want to name a significant other.

#### Data collection

Data will be collected using questionnaires according to a study-specific protocol. Timeline over data collection and information about specific questionnaires can be seen in Fig 2.

**Fig 2 pone.0299800.g002:**
[figure not shown]
SPIRIT schedule of enrolment, data collection and assessments.

*Patient data*. At baseline sociodemographic and disease-related data (e.g., stroke severity, co-morbidities) will be collected from hospital records and questionnaires. Data on patient functioning will be collected through questionnaires; cognitive function will be assessed using the Montreal Cognitive Assessment (MOCA), depression using the Patient Health Questionnaire (PHQ-2), activities of daily living using the Barthel Index (BI), recovery after stroke using a visual analogue scale, level of disability using the modified Ranking Scale (mRS), and walking ability using a single-item question. This baseline data will be collected by the research assistants.

One to two weeks after discharge, data will be collected on the primary outcome of perceived quality of care transitions using the Care Transition Measure (CTM). We will also assess secondary outcomes; health literacy using the Health Literacy Questionnaire (HLQ) and the Health Literacy Survey (HLS), stroke education retention using the Stroke Patient Education Retention questionnaire (SPER), and medication adherence using the Medication Adherence Report Scale (MARS), perceived person-centeredness using the General Person-Centered Care Questionnaire (GPCC-Q). Background and descriptive information will be collected on fatigue using a visual analogue scale, depression using the PHQ-2, level of disability using the mRS; activities of daily living using the BI, and perceived recovery after stroke using a visual analogue scale. We will also ask patients about any new or changed prescribed medications they have received after discharge, as well as perceived met and unmet needs of care and rehabilitation.

At 3 and 12 months the same instruments used at baseline and 1–2 weeks after discharge will be used to collect data on health literacy, stroke education retention, medication adherence, perceived person-centeredness, fatigue, depression, stroke severity, activities of daily living, recovery after stroke, and cognitive function. In addition, data will be collected on health-related quality of life using the EuroQol-5Dimensions (EQ-5D). We will ask patients about any new or changed prescribed medications they have received after discharge, as well as perceived met and unmet needs of care and rehabilitation.

At 12 months, data on number of recurrent strokes, unplanned hospitalizations and collected medications during the first year after stroke will be collected from Region Stockholm’s database (VAL).

*Significant other data*. After written consent, sociodemographic data, relation to the patient, home-help service, life satisfaction using the Life Satisfaction Checklist, information received, informal care supplied, and self-rated health using a visual analogue scale will be collected through a study specific protocol, and data on caregiver burden [45], and health literacy will be gathered using the HLQ. Data will be collected at 1–2 weeks, 3- and 12-months following hospital discharge.

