### Study design

We will apply a non-randomized controlled trial design, which is well suited for assessing the effectiveness of complex interventions and allows for a detailed process evaluation. Randomization at the patient level is not suitable, due to the risk of contamination. Further, the use of a non-randomized controlled trial design makes it possible to consider the roles of mechanisms, context, and the complexity of transitional care, during implementation and evaluation. We will use a research design with two intervention sites and two control sites, including multiple follow-ups over a period of one year [44] and, in two parallel phases, we will focus on evaluation of both effect and process. The SPIRIT Checklist was utilized to ensure high-quality reporting of this protocol, for detailed information see S1 Appendix.

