#### Analyses

Patients in the intervention group will be compared to the control group using intention-to-treat and per-protocol analysis. Regression models adjusting for covariates (e.g., age, gender, stroke severity, and other disease-related data) will be used for analyses of primary and secondary outcomes. Analyses will be performed and reported in accordance with the Consolidated Standards of Reporting Trials guidelines for non-randomized controlled trials [46].

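### No pre-stroke measure of unplanned hospitalizations or collected medications is named, so site differences in prior use can confound these non-primary outcomes

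*Protocol article*

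**What the plan says.** Research question 1 (Phase 1: Evaluation of effect) asks for an effect on, among others, "collected medications, medication adherence, perceived person-centeredness, functioning, recurrent stroke/TIA, healthcare utilization and caregiver burden". The data for three of these are described under Data collection, Patient data. At 12 months, from VAL, "data on number of recurrent strokes, unplanned hospitalizations and collected medications during the first year after stroke will be collected".

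The comparison is not randomised. The Study design section gives "two intervention sites and two control sites, including multiple follow-ups over a period of one year", and Setting shows one acute stroke unit and one geriatric ward in each arm. Participants admits "patients who have had a first time ever, or recurrent, stroke or TIA".

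On baseline and adjustment, the article says: "At baseline sociodemographic and disease-related data (e.g., stroke severity, co-morbidities) will be collected from hospital records and questionnaires". Cognition, depression, activities of daily living and disability are also measured at baseline. Under Phase 1, Analyses: "Regression models adjusting for covariates (e.g., age, gender, stroke severity, and other disease-related data) will be used" for the primary and secondary outcomes. The article mentions neither hospitalizations nor collected medications from before the index event, whether as a baseline item or as a covariate.

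**The concern.** When arms are formed by site, a patient's own earlier value of an outcome is usually the most direct control for differences between catchments. For most questionnaire outcomes no pre-stroke value can exist. Hospital admissions and dispensed drugs are different, because they can be counted in the same way before and after the event.

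The eligible population makes this relevant. Someone with a recurrent stroke may already take preventive drugs and may have been admitted recently; someone with a first TIA may have neither history. If the mix differs between the two pairs of sites, the difference reappears in first-year admissions and collected drugs and is read as an intervention effect. The open covariate list does not solve this by itself, because a model can adjust only for data that were obtained. The extraction period is a data-collection decision, and the article states it.

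**Working it through.** **The plan's own figure.** The concern contests no stated figure. The sample size for the primary outcome is reproduced only because its group size is used below: n = 2 × (1.96 + 0.84)² × 21² / 10² ≈ 69.2, rounded up to 70 per group, as in the Sample size section.

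**Side by side.** Outcome window for VAL: the year after stroke. Baseline sources: hospital records and questionnaires, with severity and co-morbidities as examples. Covariates: age, gender, severity and other disease-related data, as examples. Pre-stroke admissions or dispensing: not named in any of the three.

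**Illustration in admissions per patient.** The documents give no admission rates or correlations, so every input is an assumption.
- Correlation r between prior-year and following-year admissions: 0.3 to 0.6.
- Difference between arms in prior-year admissions: 0.20 per patient.
- Equal SDs in the two years, so the regression slope equals r; no true intervention effect; no other covariates.

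Carried-over bias = r × 0.20:
- r = 0.3: 0.3 × 0.20 = 0.06 admissions per patient
- r = 0.6: 0.6 × 0.20 = 0.12 admissions per patient

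Residual variance explained by the prior-year value = r²: 0.09 to 0.36, relative to a model without covariates. The gain is smaller once other covariates are in.

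**Illustration in SD units, applicable to either outcome.** Assume an imbalance d of 0.2 to 0.4 SD and a correlation of 0.3 to 0.7. Bias = correlation × d, from 0.3 × 0.2 = 0.06 SD to 0.7 × 0.4 = 0.28 SD. With 70 per group the standard error is √(2/70) = 0.169 SD. The false-positive rate of a nominal 5% two-sided test is Φ(bias/0.169 − 1.96) + Φ(−bias/0.169 − 1.96).

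| Case | Bias (SD) | False-positive rate |
|---|---|---|
| Lowest, no covariates | 0.06 | 6.5% |
| Highest, no covariates | 0.28 | 38% |
| Lowest, planned covariates capture half | 0.03 | 5.4% |
| Highest, planned covariates capture half | 0.14 | 13% |

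This is a normal approximation for what may be skewed counts, and it ignores clustering within sites. It shows only that the effect ranges from negligible to material.

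**The case against.** The article is a condensed account. The schedule (Fig 2) and the ethics-approved protocols (S2 and S3 Appendices) are not shown, and the full covariate set may properly sit in the analysis plan. The one-year period defines the follow-up for outcomes; it does not say that nothing earlier will be extracted. Co-morbidity, severity and function data are planned and capture part of the same confounding. The trial is powered on the care transition measure, and the VAL outcomes are not in the abstract's list of secondary outcomes.

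Most of this stands, and it limits the point to a recommendation. It does not dispose of it: co-morbidity and function are proxies for a patient's own prior use, and the text states a period for the VAL data without naming any look-back.

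Four stronger readings are tempting but unsupported.
- A reader might infer that VAL can certainly supply pre-stroke data. The article shows only that VAL will supply these data types after stroke; how far back it reaches, and whether earlier data are approved for use, is not stated.
- A reader might infer that drugs prescribed at discharge go unrecorded, so that a drug not collected looks like one never prescribed. The phrase that suggests this, "any new or changed prescribed medications they have received after discharge", describes a question put to patients. The hospital-record items are given only as examples and the schedule is not shown, so absence cannot be established.
- It may seem that collected medications should become a share of the drugs prescribed at discharge. That changes the estimand and may condition on something the intervention affects, since it acts during the hospital stay. At most it is a supplementary analysis.
- It may seem that adjusting for prior use would remove the confounding. That holds only if prior use is the sole confounder.

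**Conclusion.** The point holds as a recommendation on two non-primary effect outcomes: unplanned hospitalizations and collected medications. The article is neither wrong nor self-contradictory here, but it fixes a post-stroke period for the VAL data and names no pre-stroke value in a comparison where sites define the arms.

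The size is not determined by the documents. Under the assumed correlations and an assumed gap of 0.20 prior admissions, 0.06 to 0.12 admissions per patient is an upper range that applies before the planned covariates; they would lower it by an unknown amount. Recurrent stroke is left out of the baseline argument, although the same sentence covers it, because stroke history may already be collected as disease-related data. The primary outcome is not affected.

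**What to change.** In Phase 1, Data collection, extend the planned VAL extract to the 12 months before the index stroke or TIA for unplanned hospitalizations and preventive drugs collected. This is conditional on VAL holding those records and on ethics approval and consent covering them. In Phase 1, Analyses, name each outcome's own prior-year value as a covariate in its regression model, alongside the covariates already planned. If the look-back is not possible, say so and report the two effects as open to confounding by prior use.

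The cost is a possible extension of the ethics approval and consent text, and slightly more data handling. The outcome definitions stay as they are.

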#### Sample size

Results from our pre-studies show that participants had a mean of 62 points in the care transition measure and standard deviation of 21. Based on the estimation that satisfaction will be a mean of 72 in the person-centred multicomponent care transition, we will need to recruit 70 patients (80% power, p = 0.05, 2 sided). Allowing for 20% drop-out, we will need to recruit in total 84 patients per group, 168 patients in total.

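### Minor arithmetic error: 84 per group is 70 × 1.2, which keeps 70 evaluable patients only up to 16.7% drop-out, not the stated 20%

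*Protocol article*

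**What the plan says.** The calculation is in the Sample size section under Phase 1. The sponsor's pre-studies supply the comparator figures: "participants had a mean of 62 points in the care transition measure and standard deviation of 21". The target for the intervention is that "satisfaction will be a mean of 72 in the person-centred multicomponent care transition". From these the section concludes "we will need to recruit 70 patients (80% power, p = 0.05, 2 sided". It does not say there whether 70 is per group or overall. The next sentence adds the allowance for losses: "Allowing for 20% drop-out, we will need to recruit in total 84 patients per group, 168 patients in total".

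The section gives no formula for the allowance and does not say by which visit the 20% is expected to be lost. The Data collection section places the primary outcome, the Care Transition Measure, one to two weeks after discharge. Other follow-up runs to 12 months.

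**The concern.** A drop-out rate is a share of the patients recruited. To be left with a required number after that loss, one divides the number by the proportion retained. The step from 70 to 84 instead adds 20% of the required number to itself, which gives a smaller target.

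On the plan's own terms, three statements then do not fit together: 84 recruited per group, 20% lost, and 80% power from 70 evaluable per group. What is at stake is whether the stated recruitment target supports the stated power for the primary outcome, and by how much it falls short.

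**Working it through.** **Inputs, all from the Sample size section**

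- Means of 62 and 72, so a difference of 10 points.
- "standard deviation of 21", so a standardised difference of 10/21 = 0.476.
- "80% power, p = 0.05, 2 sided".
- "Allowing for 20% drop-out".
- Equal groups (84 and 84, 168 in total).

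**Step 1. Reproduce the 70.** For a two-sided comparison of two means,

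n per group = 2 × (1.960 + 0.842)² × (21/10)² = 69.2, rounded up to 70.

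The t-test version gives 70.2. Either way the stated 70 is recovered, and it must be per group. If 70 were the total (35 per group), power would be about 51% by the normal approximation. A one-sided test would need 55 per group, so it does not match.

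**Step 2. Reproduce the 84.** 70 × 1.2 = 84 exactly, and 2 × 84 = 168. Division by the proportion retained gives a different answer: 70/0.8 = 87.5, so 88 per group and 176 in total. Rounding does not explain the gap. Starting from 69.2 or 69, division by 0.8 gives 87 per group; starting from 71 it gives 89. None gives 84.

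**Step 3. What 84 leaves.** 84 × 0.8 = 67.2, so about 67 evaluable per group, 3 short of 70. The largest loss that still leaves 70 is 1 − 70/84 = 0.167, or 16.7%.

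**Step 4. Power.** By the normal approximation, power = Φ(10 / (21 × √(2/n)) − 1.960).

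- n = 67: 10 / (21 × 0.1728) = 2.756; 2.756 − 1.960 = 0.796; Φ = 78.7%.
- n = 70: 10 / (21 × 0.1690) = 2.817; 2.817 − 1.960 = 0.857; Φ = 80.4%.

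| Evaluable per group | Normal approximation | t-test |
|---|---|---|
| 67 | 78.7% | 78.1% |
| 70 | 80.4% | 79.9% |

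The loss is 80.4 − 78.7 = 1.7 points by the normal approximation and 79.9 − 78.1 = 1.8 points by the t-test.

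**The case against.** The strongest reply is that the error hardly matters. Three evaluable patients per group and less than 2 points of power are small beside the uncertainty in the assumed 10-point difference and the standard deviation of 21. On the t-test the base of 70 is itself at the rounding edge: it gives 79.9%, and strict rounding of 70.2 to 71 would lead to 89 per group rather than 88. The formula is also a plain comparison of two means, whereas the Analyses section plans covariate-adjusted regression, and each arm consists of only two sites. Eight more patients would not make 80% an exact figure for this design. All of this stands, and it is why the point is minor.

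A second reply concerns timing. The 20% may be meant as the cumulative loss to 12 months. In that case fewer would be missing one to two weeks after discharge, and any loss up to 16.7% leaves at least 70 per group. This also stands. A reader might infer from the arithmetic that the trial is underpowered, or that the primary analysis will certainly miss 80%. The document does not support that, because it does not tie the 20% to the primary assessment.

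Neither reply makes the sentence correct. The section sets the 20% beside the sample size for the primary outcome without qualification, and the target should follow from the rate it names. Reading the 20% as a margin added on top would account for 84, but the text calls it drop-out, and such a margin covers only 16.7%. Covariate adjustment may recover some power, but the section claims no such gain and gives no correlation from which to compute one. Nor is this a matter of an article leaving out detail, since the figure is stated and does not follow from its own inputs.

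**Conclusion.** The recruitment figure is wrong as written, and the error is minor. With 20% drop-out, 84 per group leaves about 67 evaluable patients rather than 70, and power is about 78.1% (t-test) or 78.7% (normal approximation) rather than the stated 80%.

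This rests on the section's own means, standard deviation, significance level and equal groups, on reading 70 as per group, and on the full 20% being lost by the primary assessment. If loss by then is 16.7% or less, the 70 is kept.

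The error does not affect the design, the choice of outcome, the planned analysis or the interpretation of a result. It does not by itself oblige the sponsor to recruit more patients.

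**What to change.** Correct the sentence on drop-out in one of two ways.

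1. **Keep 168 in total (preferred, no cost in patients).** State that 84 per group retains 70 evaluable patients up to 16.7% drop-out, and that at 20% drop-out power is about 78–79%. This is one reworded sentence.
2. **Preserve 80% power at 20% drop-out, if the sponsor so chooses.** Restate the target as 88 per group, 176 in total. This costs 4 more patients per group, 8 overall.

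As an editorial matter, the same edit can add that the 70 is per group, and by which assessment the 20% is expected to be lost.

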#### Analyses

Patients in the intervention group will be compared to the control group using intention-to-treat and per-protocol analysis. Regression models adjusting for covariates (e.g., age, gender, stroke severity, and other disease-related data) will be used for analyses of primary and secondary outcomes. Analyses will be performed and reported in accordance with the Consolidated Standards of Reporting Trials guidelines for non-randomized controlled trials [46].

### Phase 2: Process evaluation

The overall aim of the process evaluation is to explore contextual moderators, implementation aspects, and mechanisms of impact that might explain the potential effects of the multi-component care transition intervention.

Research questions:

2. What are the patients’, significant others’, and healthcare professionals’ experiences of the intervention components and the implementation process?3. How does the intervention get adapted and implemented in practice?4. What contextual factors and mechanisms of the intervention can likely explain the potential effects of the intervention?

#### Design

Mixed-method process evaluation.

#### Participants

Qualitative interviews and observation: We will use theoretical sampling [47] to be able to explore the behaviours and interactions between patients, significant others and healthcare professionals in different settings and how the emergence of the system contributes to how the intervention behaves, i.e., is operationalized and adapted in practice.

Quantitative data: All healthcare professionals at the intervention sites will be asked to participate in data collection on implementation aspects and fidelity to the intervention.

#### Data collection

Patients and significant others: Semi-structured interviews with open-ended questions will be held with patients and significant others. Patient and significant other interviews will target their experiences of the care transition, including how they understood information and their perspectives on their interaction with healthcare professionals. For patients at intervention sites, interviews will also target intervention components. To support theoretical sampling and theory building, data will be collected in an iterative, comparative, and interactive way [48].

Healthcare professionals: Semi-structured interviews and focus groups with open-ended questions will be conducted. The healthcare professionals will be asked to describe their experiences of the care transition; and for healthcare professionals in intervention sites, the use of the intervention in everyday clinical practice including the implementation will be explored. Data from healthcare professionals on the process of implementation and maintenance of the intervention will be collected with the Normalization MeAsure Development Questionnaire (NoMAD), which is based on the NPT [49]. NoMAD will be used from the intervention start to iteratively assess and monitor the implementation of the intervention. Data on dose and fidelity to the intervention components will be collected using self-reports from the healthcare professionals.

Patients, significant others, and healthcare professionals: The interaction between patients, significant others, and healthcare professionals will be observed at the hospital and during encounters with the neurorehabilitation team at home. Observations and subsequent interviews will be used to understand how the intervention components are operationalized by healthcare professionals, to capture the interaction between intervention components and the ways that healthcare professionals interpret and respond to them. We will explore the mechanisms of how and why intervention components give rise to outcomes and how contextual moderators influence the implementation, intervention components and mechanisms. Further, interviews on implementation aspects will be guided by NPT and will focus on how people make sense of the intervention (coherence), how people make it work in practice (collective action), how people assess and decide whether it is worth the effort (reflexive monitoring), and how healthcare professionals get involved and stay committed (cognitive participation) [41]. Field-notes and analytical reflections will be made by the responsible researchers.

All interviews and observations will be audio-recorded and transcribed verbatim.

Data on dose and fidelity to the intervention components will also be collected using administrative data from the booking system and from the patient records.

